6.2.1 Database infrastructure

The project will use a distributed electronic database (managed by UNEXE) during the project that will store all the downloaded cohort data and clinical trial data. Within the clinical trials, UNEXE will be in charge of the set-up and management of the database. The equivalent of anonymised electronic Case Report Form (eCRF) data will be set-up and entered in a Qualtrics, which is fully validated. The eCRF and associated database will be automatically populated from the responses entered by participants via websites and app platform: data will be encrypted and pseudonymised immediately after downloading from the website or app and then stored securely and converted into an electronic database suitable for analysis. Lead Researcher will code-link personal information to the rest of the data. This coding spreadsheet will be password protected and only accessed by the lead researcher. The rest of the research team will only have access to the aggregated data. Data will be routinely backed-up during and after the project to ensure the availability of all the information.

### 6.2.2 Data Management Plan

The Data Management Plan will describe how the data will be exploited, checked, shared, curated and preserved. Thus, the procedure for granting access will be detailed and the mechanisms to access the data after the project will be described. It should be noted that no data will be collected or used without the explicit informed consent of the participants.

### 6.2.3 Data format and types

Standard data formats will be used during the project and will be compliant with Clinical Data Interchange Standards Consortium – Clinical Data Acquisition Standards Harmonisation (CDISC-CDASH) standard. Data types will include Volunteer data: Demographics and information provided by participants on the study questionnaires.

### 6.2.4 Data exploitation

All information will have a digital format that will be handled in accordance with European and national data protection regulations. A mechanism to request access, mine, exploit, reproduce or disseminate data generated in the framework of this project will be put in place.

### 6.3 Data protection/confidentiality

### 6.3.1. Data protection

The conduct of the project will comply with GDPR. Adequate measures to ensure data protection and confidentiality will be duly taken into account by the research team. Local and national rules on data protection will be followed, and no personal information of participants will be transferred unless such transfer is essential for the conduct of the trial.

All research data will be stored on a UNIEXE database linked to the unique identifier ID to pseudonymise all information collected. Before taking part, all participants are provided with Participant Information Sheet which also includes information on privacy policy. At initial screening potential participants are not asked to provide their email addresses contact details (i.e., mobile phone number). If participants are eligible to take part after initial screening, they are asked to complete the second screening, which also serves as the baseline measure, sociodemographic questionnaire and provide their email address and mobile phone number. Phone numbers are collected to send reminders to participants. The database contains all the baseline (i.e., second screening) and follow up data collected from the EDC system. The codes linking contact information with the database containing outcomes will be destroyed as early as is legally required (no earlier than all data being archived – 3 months post study endpoint) – data (including participant details and consent) may need to be retained and not deleted for a longer period due to future research indicators that may require researchers to contact the individual or actions taken by participant against the research. This approach has proven successful in prior digital interventions for wellbeing and has been approved by multiple institutional and National Health Service research ethics in the UK; adaptations will be made as necessary for specific local ethical requirements.

### 6.3.2 Digital Information

Files containing digital information will be encrypted with password-protection where appropriate and stored on the UNIEXE secure network (not a local ‘C’) drive. Where local copies are required for processing or transfer preparation, it will be ensured that the target workstation is compliant with all UNIEXE security policies and that they are followed. This is particularly important for laptops/netbooks/portable workstations, especially about encryption and will be confirmed by UNIEXE before transferring data. The relevant university guidelines and policies will be followed (e.g., the UNIEXE Information Governance (https://www.exeter.ac.uk/departments/cgr/ig/policy/), Security Policy (https://www.exeter.ac.uk/departments/cgr/ig/informationsecurity/), Computing Regulations (https://www.exeter.ac.uk/staff/policies/calendar/part1/otherregs/its/) and University guidelines for portable and removable devices (https://www.exeter.ac.uk/media/universityofexeter/it/recordsmanagementservice/policydocuments/Information_Security_for_Portable_and_Removable_Media_Devices_Policy_4.0.pdf). Participants identifiable data will not be stored on home computers, personal laptops, unencrypted memory sticks, CDs, handheld devices, digital cameras or other imaging equipment even if they are password protected. An encrypted memory stick may be used if required.

All data generated will be stored by UNIEXE in encrypted and password-locked files behind a secured firewall operating within a university environment with state-of-the-art safety protection measures, and transmission of information via electronic means will be performed using encrypted data files. The exact process for data storage and encryption for the data processors are outlined in the data management plan.

### 6.3.3. Participant data

Participant confidentiality and welfare will always be maintained as the highest priority. All research staff with access to data is subject to professional secrecy during and after the trial. During the course of the project, we do not anticipate any sharing of individual participant data from this clinical trial outside of the UNIEXE.

Anonymised data (including Armed Forces served in and date of leaving, socio-demographic information, platform usage information) will not be deleted until the completion of the analysis of the data plus the mandatory period for retaining research data (at least ten years in the UK).

The database containing link codes, which connect participants to their study data, will be retained for 3 months after the study's completion. This period ensures participants can exercise their right to withdraw their data and addresses any potential actions taken by participants concerning the research. After this period, this database will be securely and permanently deleted.

###

### 6.3.4 Responsibility

The UNIEXE as sponsor of the trial is the data controller. The controller has the responsibility to ensure that the security and access arrangements for the database comply with the Data Protection Act (2018), and that all data processing and locally held personal data are registered with the host institution according to their employer’s processes. Because this trial involves the processing of personal information the Information Commissioner’s Office (ICO), will be notified accordingly.

Legal data transfer agreements will be written and signed between the data controller and data processors prior to any participant being recruited, where appropriate. These agreements will be confirmation that the data processors will adhere to GDPR regulations, which protect and safely store participant personal and outcome data.

A common data protection and privacy policy authorised by the sponsor, and the UNIEXE data protection team will be available on the study website. The screening website will also email this policy to consenting participants with the information sheet and consent form or provide it as a download.

### 6.3.5 Data monitoring

Data will be accessed by the researchers on a regular basis (typically at least weekly) to check recruitment numbers and data quality and to monitor that all processes are working correctly. Detailed checks will occur early in the project to confirm that all systems are working properly. To download data the Lead Researcher has to login via username and password.

### 6.3.5a Data monitoring committee

An initial meeting held with the DMC determined the role of the DMC and frequency of reporting throughout recruitment and study follow up. The Chair of the DMC ([name]) will be updated weekly as to study progress and informed regarding adverse events. He will organise meetings to discuss study progress with wider members of the DMC comprising a female armed forces officer, NHS armed forces veterans service lead, and regional commissioner. The DMC is independent of the sponsor and funder. At the end of the study, prior to the randomisation code being broken, a written draft results section will be presented to the DMC alongside the aggregated data to ensure compatibility.

### 6.3.6 Breach of confidentiality

Occasionally records containing personal data that should not have been disclosed, (e.g. an e-mail with a data file containing identifiable details) may be received by a staff member from an internal or external source. In such situations, the member of staff should contact the person who sent the data and make them aware of the breach of confidentiality. The records received should be either promptly deleted or any identifying details thoroughly erased. All suspected breaches would be investigated, documented in the study file and reported to the Sponsor as appropriate, following an established data breach the UNEXE procedure will be followed.

### 6.4 Trial documentation and archiving

The materials for the trial will be submitted with this study protocol.

Source documents and trial-related electronic and other data. Stored safely and in accordance with the requirements of the GDPR and UK Data Protection Act (2018), no longer than legally required (for a minimum of ten years) or as stipulated by the Sponsor’s requirements.

Data Access: Post-analysis, the final anonymised dataset will preferentially be stored in Open Research Exeter (ORE), the UNIEXE open access repository.

Interoperability: Source data will be stored in Microsoft SQL server, formatted to maximise fidelity. This can be transposed and converted during the analysis stage into any format required. For the Open Research Exeter repository XML or CSV with a separate data dictionary is recommended.

Archiving: Items submitted to ORE will be retained indefinitely. ORE content is securely held on UNIEXE servers and regularly backed up according to current best practice. The ORE team will also ensure continued readability and accessibility of content, including the migration to new file formats where necessary.

### 6.5 Authorisation of Participating Site

The study is online and solely located at the UNIEXE who will act as sponsor to the research programme and authorise after ethical approval has been granted. The Chief Investigator and Lead Researcher are familiar with applicable Standard Operating Procedures, risk assessment procedures, and agree that Good Clinical Practice (GCP) and General Data Protection Regulation (GDPR) standards will be followed.

### 7. PARTICIPANT INCLUSION/EXCLUSION CRITERIA

**Table 8 Inclusion/Exclusion criteria**

| **Inclusion** | **Exclusion** |
| --- | --- |
| **Initial screening** | |
| Aged 18 or over | AGED <18 |
| Ex-servicewoman | Not ex-servicewoman |
| Resident in Great Britain | Not resident in Great Britain |
| Ability to read and understand English | Unable to read and understand English |
| No history of psychosis, mania, substance/alcohol dependence | History of psychosis, mania, substance/alcohol dependence |
| Ability to download app | Not able to download app |
| Access to smartphone with internet access | No access to smartphone or access internet |
| Not changed or started ADM in last month | Changed or started ADM in last month |
| Not currently receiving mental health support | Currently receiving mental health support |
| **Second screening/Baseline** | |
| PHQ-9=>5; <20 | PHQ-9<5; =>20 |
| GAD7<15 | GAD7=>15 |
| Suicide risk: PHQ-9 Q9=<1 | Suicide risk: PHQ-9 Q9=>2 |

### 8. TRIAL PROCEDURES

### 8.1 Participant identification

We will recruit from participating Armed Forces Veteran specific community and charitable organisations, social media and through opportunistic sampling. Posters, emails, websites, presentations, and social media will all advertise the study to female veterans who wish to tackle anxiety and depression. Recruitment of participants will be through following routes commonly adopted and used by the community/charitable groups supporting the study such as:

• Local promotion and email circulars commonly adopted by the community/charitable organisations and local promotion (e.g. posters, emails, newsletters, signposting by staff).

• Multiple traditional and social media (posting and advertising on Facebook, LinkedIn, Instagram, SnapChat, Google, MySpace, X/Twitter, TikTok, through media influencers/vloggers, etc adjusted by cost/frequency as needed); social media analytics will be used to enhance recruitment.

• Snowballing approaches.

### 8.2 Screening

Participants will be screened online - those under 18, not an EXSW, not resident in the UK, history of psychosis, mania, substance/alcohol dependence, no access to smartphone or internet, changed or started ADM in the last month, and currently receiving mental health support will automatically be screened out during the first screening. Website users who report having current risk, based on PHQ9 and GAD 7 during the second screening will be taken to the feedback screen where they will be advised we are sorry to hear that they are feeling that way, their safety is of our utmost concern, to please contact their GP or other Armed Forces related risk management organisation and to give them sources of online help and support. Contact details for appropriate Armed Forces specific organisations to seek further help and support risk management have been informed by the ex-Armed Forces Veterans Lead for the NHS and co-investigator on the research.

### 8.3 Consent

Potential participants will be initially routed to, or seek out, the UNIEXE Qualtrics page and will be provided with the Participant Information Sheet. If interested in participating, they will select a checkbox that takes them to the Consent Form and data protection policy to review on the trial electronic platform. Study eligibility and inclusion criteria will be clearly stated, and participants asked to electronically sign the Consent Form and date. The Consent Form asks for consent to undertake the initial and secondary screening, taking part in the trial as well as confirmation that the participant understands the nature of the study and meets inclusion criteria. Participants are asked to confirm that they meet each criterion. If eligible, participants will be asked to provide an e-mail address and mobile phone number.

If a participant completes the Consent Form and is eligible for the trial, they will be given an e-mailed confirmation that they are in the study, a unique study participant trial number and instructions indicating how, as per randomisation scheme, to download IonaFFV or Iona SHAM CONTROL on either an Android or Mac (IOS) based mobile phone. They are also provided with contact details (email, and/or telephone number as available) for the Lead Researcher if further study information is wanted or they are struggling to download IonaFFV or Iona SHAM CONTROL.

### 8.4 Randomisation scheme

The feasibility RCT will follow MRC Complex Interventions Guidelines and relevant CONSORT reporting requirements with a pre-registered trial protocol. Randomisation will be in blocks of 3 with randomisation to the 2 arms (IonaFFV vs Iona SHAM CONTROL) conducted automatically by Qualtrics survey platform to minimise selection bias and maintain methodological rigor. Following randomisation IonaFFV or Iona SHAM CONTROL will be automatically sent a link to download the app.

### 8.6 Method of implementing the randomisation/allocation sequence

Participants will be randomised by pseudorandom number generation. Eligible participants will receive an email confirmation which provides a download link and unique participant code to each participant accepted into the trial, and they will be prompted to download the app as soon as possible. Once selected according to the randomisation sequence either IonaFFV or Iona SHAM CONTROL, participants will download the app on their phone. Participants are blinded to the randomisation.

Should a participant fail to download the app and enter the code, an automated sequence of emails at the rate of 1 per day over a 7-day period will be sent to the participant reminding them to do so and reiterating the download and sign-up instructions. After this time no further contact with the participant will be made.

Detailed procedure for randomisation:

1. Participants are randomised in blocks of 3 (30 participants per arm) into the 2 arms (IonaFFV versus Iona SHAM CONTROL) on an intention-to-treat basis.
2. Block randomisation will continue until 60 (30 each arm) are randomised. As eligible participants complete the initial screening and demographics questionnaire they will be randomised in blocks of 3 to either the control or intervention arm by the Postdoctoral Research Associate or the Graduate Research Assistant.

3.       The system will record the allocation and the date randomised.

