### 8.9 Trial assessments

Assessment will take place at baseline and then at 6 weeks post treatment start (equating to end of treatment) and 10-weeks post baseline representing the study endpoint. At both of these timepoints the participant will receive a request to complete the outcome measures with a URL included to take them to the UNIEXE Qualtrics page. The results of the assessments are only to collect research data for the trial and will not be provided to anyone outside of the study. The only exception to that would be if a participant indicates suicide risk and asks us to provide their assessment results to their medical practitioner. They would need to give written consent for this and provide us with the contact details to do so.

At the end of treatment, all participants will be asked to complete the MAUQ

to determine the acceptability and usability of the app.

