**Table 9 Assessment Schedule**

| **Procedures** | **Initial screening** | **Baseline (second screening)** | **6 weeks post initial app engagement** | **4 weeks follow-up**  **(10 weeks post initial app engagement)** |
| --- | --- | --- | --- | --- |
| Informed consent | Yes | Yes | No | Yes |
| Demographics | Yes | Yes | No | No |
| Mental Health History | Yes | No | No | No |
| Eligibility assessment | Yes | Yes | No | No |
| Randomisation | No | Yes | No | No |
| Access to intervention | No | No | Yes | No |
| Assessment of wellbeing and depression | No | Yes | Yes | Yes |
| Assessment of current functioning | No | Yes | Yes | Yes |
| Assessment of usability and engagement | No | No | No | Yes |
| Feasibility outcomes | No | No | No | Yes |
| Adverse event assessments | No | No | Yes | Yes |

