### 8.12 Withdrawal criteria

At any time, participants can choose whether they want to stop using the IonaFFV or Iona SHAM CONTROL intervention, or if they want to withdraw from the trial completely (including all assessments). A log will be kept of the participant number and date of all withdrawals from the trial. Participants who met the inclusion criteria at baseline will not be replaced. Participants that did not meet the criteria at baseline can be replaced and their data removed from the data set. Participants who withdraw from the trial will not be followed up. Once a participant withdraws from the study, they will still be able to use the app until the end of the study period if they choose.

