### 11.3 Statistical analysis plan

A detailed statistical analysis plan (SAP) is to be produced; the main points of the statistical analysis are summarised here. All participants will be included in each analysis, separated by arm. Missing data will be reported descriptively. No imputation will be performed due to the feasibility nature of the study, but patterns of missingness will be explored to inform future trial design.

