### 11.4 Summary of baseline data and flow of patients

The analysis and presentation of the trial will be in accordance with CONSORT guidelines (Schulz et al., 2010). Recruitment, intervention uptake, outcome completion rates and attrition will be reported (with 95% CIs) and shown on a study flow diagram.

Participants may elect to withdraw from the study if they wish to do so at any time and for any reason (including perceived harms or lack of efficacy of intervention). This can be easily done by discontinuing use of the randomised app.

Participants will be withdrawn from the study entirely if discovered as ineligible at the time of recruitment. As a self-help psychological intervention, we do not anticipate significant iatrogenic effects or side-effects requiring individual discontinuation.

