### APPENDIX

Appendix 1: Feasibility Outcomes

| **Feasibility Outcomes** | | | | |
| --- | --- | --- | --- | --- |
| Number of people accessed study web site | |  | | |
| Number of people consented | |  | Report by demographics | |
| Number of people randomised | |  | Report by demographics | |
| Blinding randomisation maintained | | Yes | | No |
| Study arms | |  | | |
| Iona FV | Number downloaded app |  | | |
|  | Number completed baseline outcome measure | Data completion of each item for each outcome measure | | |
|  | Number completed treatment |  | | |
|  | Number completed end of treatment outcome measures | Data completion of each item for each outcome measure | | |
|  | Number completed final outcome measures 10 week post treatment start | Data completion of each item for each outcome measure | | |
| Iona SHAM CONTROL | Number downloaded app |  | | |
|  | Number completed baseline outcome measure | Data completion of each item for each outcome measure | | |
|  | Number completed treatment |  | | |
|  | Number completed outcome measures at 6 weeks post baseline | Data completion of each item for each outcome measure | | |
|  | Number completed final outcome measures 10 week post treatment start | Data completion of each item for each outcome measure | | |

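### Section 8.6 ends all contact with randomised women who do not download the app, so as written they never receive the week-6 and week-10 questionnaires, against the intention-to-treat aim

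*Protocol*

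**What the plan says.** **Contact.** Sections 6.1 and 8.4 place randomisation before download. Section 8.6 sends a non-downloader one email a day for seven days and then states: "After this time no further contact with the participant will be made". The same section describes the randomisation as intention-to-treat. Section 11.3 says "All participants will be included in each analysis, separated by arm" and rules out imputation. Section 8.5 relies on emails and texts to limit attrition bias.

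**Stopping the app.** Section 11.4 says of withdrawing from the study: "This can be easily done by discontinuing use of the randomised app". Section 8.12 adds: "Participants who withdraw from the trial will not be followed up". Yet 8.12 opens by giving participants two separate choices, to "stop using the IonaFFV or Iona SHAM CONTROL intervention, or if they want to withdraw from the trial completely".

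**Visit timing.** Three origins appear:
- App or treatment start: Table 9 ("6 weeks post initial app engagement"), Table 12 and section 10.4.
- Baseline: sections 8.10 and 10.5 and the feasibility table in 10.7.
- Randomisation: the study summary in section 5.

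Section 8.9 uses two of them in one sentence: "Assessment will take place at baseline and then at 6 weeks post treatment start (equating to end of treatment) and 10-weeks post baseline".

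**The concern.** Download happens after randomisation and may be related to outcome. If questionnaires go only to women who downloaded, outcome data are conditional on that event, and the set of all randomised women that 11.3 promises to analyse cannot be assembled.

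The larger stake is feasibility. Measure completion and drop-out are primary outcomes (section 5, Table 11, section 11.5) and are meant to inform a definitive trial. That trial needs to know how many randomised women answer questionnaires when asked, whether or not they take up the app. Under 8.6 the question is never put to non-downloaders, and answers not requested at weeks 6 and 10 cannot be obtained later.

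The other two inconsistencies make this worse. Under the app-start clock a woman who never starts has no due date. Under one reading of 11.4 with 8.12, women who stop using the app could also be left out of follow-up.

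**Working it through.** The protocol has no sample size calculation (11.1) and gives no dropout or non-download rate, so there is no stated figure to reproduce. The planned size, 60 with 30 per arm, is from section 5. Every rate *d* below, the share of randomised women who never download, is an assumption.

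**1. Can the passages all be followed?** A non-downloader is randomised, so 11.3 includes her. Under 8.6 she is not contacted at weeks 6 or 10, so she has no outcome, and 11.3 forbids imputing one. The three statements cannot all be carried out.

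**2. Cap on completion.** Highest possible completion over all randomised = 1 − *d*: 95%, 90%, 80% and 70% for *d* = 5%, 10%, 20% and 30%.

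**3. Non-uptake mixed with non-response.** Take *d* = 20%, so 48 of 60 download, and 90% response among them: 0.9 × 48 = 43.2, about 43.
- Over all randomised: 43/60 = 71.7% (Wilson 95% CI 59.2 to 81.5).
- Over downloaders: 43/48 = 89.6% (77.8 to 95.5).
- If half of the 12 non-downloaders had answered when asked: (43 + 6)/60 = 81.7%.

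The third figure is closest to what a definitive trial needs, and the protocol as written cannot observe it.

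**4. Effect size.** Assume equal *d* in both arms, no benefit without download, and arms otherwise alike. If the effect among those followed up is τ, the intention-to-treat effect is (1 − *d*)τ, and the ratio is 1/(1 − *d*).
- *d* = 10%: 1/0.9 = 1.11, or 11% too large.
- *d* = 20%: 1/0.8 = 1.25, or 25% too large.

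**5. Consequence for a later trial.** Assume an observed PHQ-9 difference of 2.5, SD 5, 90% power and two-sided 5%. The observed effect gives 85 per arm. The intention-to-treat effect needs 104 per arm at *d* = 10% (difference 2.25) and 132 at *d* = 20% (difference 2.0).

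**6. Bias with no true effect.** If non-downloaders' mean outcome differs from downloaders' by a gap Δ that is the same in both arms, the bias in the arm difference is (difference in *d* between arms) × Δ. With Δ assumed to be 2 to 4 PHQ-9 points:
- Equal *d*: 0.
- 10% against 20%: 0.1 × 2 = 0.2 to 0.1 × 4 = 0.4 points.
- 10% against 30%: 0.4 to 0.8 points.

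The sign reverses if the arms are exchanged.

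**7. Clock.** Suppose a woman downloads on the seventh day of reminders, taken as 7 days after baseline. Under the sentence in 8.9, her 6-week visit falls on day 7 + 42 = 49 and her 10-week visit on day 70. They are then 21 days apart, not the 28 that a 4-week follow-up implies.

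**The case against.** **The cut-off may concern download reminders only.** The sentence directly follows the description of those emails, and 8.7 and 8.9 have Qualtrics sending follow-up requests and reminders. That may be the intention, but the text does not limit it, and whoever sets the survey triggers needs wording that does. Section 8.11 does not help: its drop-out payment names only women who leave after downloading.

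**The comparison is exploratory, and counts over 60 stay arithmetically correct.** Both are true. Appendix 1 already counts downloads and treatment completion by arm, and 11.4 reports uptake, completion and attrition. The problem is therefore narrower than a failure to record non-use. What is lost is the response of non-downloaders to a questionnaire request.

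Four stronger readings are tempting, and the documents do not support them:
- *Stopping the app counts as withdrawal.* Section 11.4 can be read as naming a route for a withdrawal the participant has chosen, and 8.12 separates the two acts. This is a contradiction to reconcile, not a settled rule.
- *Data come only from women who engage.* The 8.6 cut-off applies to women who never download and enter the code. No passage makes the later requests depend on continued use.
- *The arms run on different clocks.* Appendix 1 labels the sham row "Number completed outcome measures at 6 weeks post baseline" and the IonaFFV row as end of treatment, but the 10.7 table equates the two labels for both arms.
- *The comparison and completion rates are therefore biased.* They are exposed to bias. With equal non-download and no true effect, the bias in the arm difference is zero.

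On timing, baseline and randomisation nearly coincide if randomisation follows the baseline questions at once (6.1). The discrepancy that matters is app start against either of these.

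**Conclusion.** The point holds in this form. Followed exactly, 8.6 denies randomised non-downloaders both follow-up questionnaires, which cannot be squared with 8.5, 11.3 or the intention-to-treat statement in 8.6 itself. Completion over all randomised cannot exceed the download rate.

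The bias in the arm comparison cannot be sized from the protocol. The 11% and 25% figures are illustrations: they require equal non-download in the two arms and no benefit without download, and they cover never-downloaders only, not women who start and then stop. The contradiction between 11.4 and 8.12 and the three visit clocks are separate drafting faults that bear on the same follow-up. The correction is warranted despite the exploratory aim, because the data lost are themselves among the trial's primary outcomes and cannot be recovered.

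**What to change.** - **8.6:** limit the 7-day cut-off to download reminders.
- **8.6 and 8.9:** send the week-6 and week-10 Qualtrics requests and reminders to everyone randomised, whatever her app use, unless she withdraws from assessments. The removals for risk in 11.8 and 13.4 are a separate matter and are not addressed here.
- **Timing:** count both assessments from the date of randomisation, which 8.6 already records. Align 8.9, 8.10, 10.4, 10.5, Tables 9 and 12, the 10.7 table and Appendix 1, using the same row labels in both arms.
- **11.4 and 8.12:** reconcile them so that stopping the app does not by itself end follow-up.
- **Reporting:** give completion over all randomised and over downloaders, by arm. Count withdrawal from follow-up separately from the download and treatment-completion counts already in Appendix 1.

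**Cost.** Wording, survey triggers and a few more automated messages. Email addresses and phone numbers are already collected before randomisation (6.3.1). Non-starters who respond would add vouchers of at most £30 each (8.11), and 8.11 should say whether they qualify. The event reporting period in 12.4 begins at first use of the app, so it must be reconciled with PHQ-9 scores collected from women who never start.
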